## Abstract

**Background:**

Preterm birth accounts for 75% of perinatal deaths and more than 50% of long-term neurological disabilities. For a singleton pregnancy, progesterone treatment is effective in prevention of preterm birth in women with an asymptomatic short cervix or a history of preterm birth. However, a large proportion of preterm births still is not currently preventable. The aim of this study is to determine whether early universal use of oral progesterone before 14 + 0 weeks of gestation can prevent preterm birth better than universal screening of cervical length at 18 + 0 to 23 + 6 weeks of gestation, followed by progesterone treatment in those with a short cervix in singleton pregnancy.

**Methods:**

This is a multicenter, randomized, double-blind, placebo-controlled trial registered with ClinicalTrials.gov on 12 February 2018. Eligible consecutive pregnant women with singleton gestation attending antenatal outpatient clinics will be recruited after receiving counseling and signing the written consent form. Transvaginal cervical length measurement will be performed at recruitment (before 14 + 0 weeks of gestation) and between 18 + 0 and 23 + 6 weeks of gestation. After randomization, women will be randomly assigned to either the treatment group (oral dydrogesterone 10 mg three times daily) or the placebo group, and medication will be started before 14 + 0 weeks of gestation. Assigned groups will be unblinded if the cervical length is ≤ 25 mm between 18 + 0 and 23 + 6 weeks of gestation, and the management option for short cervix will be discussed (oral progesterone, vaginal progesterone, or cervical cerclage). The primary outcome is preterm birth before 37 + 0 weeks of gestation.

**Discussion:**

Progesterone is used extensively in part of the in vitro fertilization program as luteal phase support, and it is not associated with teratogenicity. Universal progesterone supplementation may be a better approach to prevent preterm birth. This large, multicenter, randomized, double-blind, placebo-controlled trial will provide the best evidence, leading to the best strategy for the prevention of preterm birth.

**Trial registration:**

ClinicalTrials.gov, NCT03428685. Registered on 12 February 2018.

## Background and rationale

Preterm birth (PTB), defined as birth before 37 completed gestational weeks, is a major challenge to perinatal health. It accounts for 75% of perinatal deaths and more than 50% of long-term neurological disabilities [1, 2], and it is the second most common cause of death in children under the age of 5 years [3]. Neonates born preterm are at risk of respiratory distress syndrome, chronic lung disease, retinopathy of prematurity, necrotizing enterocolitis, intraventricular hemorrhage, and sepsis in the short term, as well as cerebral palsy, motor and sensory impairment, learning difficulties, and increased risk of chronic disease in long run [4]. The estimated societal cost of PTB is $26 billion annually in the United States alone. The cost of PTB is inversely related to gestational age at birth. Costs stand at over US$100,000, US$40,000–US$100,000, US$10,000–US$30,000, and below US$4500 for babies born at extreme prematurity (< 28 weeks of gestation), early prematurity (28–31 weeks of gestation), moderate prematurity (32–34 weeks of gestation), and late prematurity (35–36 weeks of gestation), respectively [5]. On the basis of evaluation of data from 184 countries, the estimated global mean PTB rate is approximately 11.1%, ranging from 5% to 18% in different countries [6].

For singleton pregnancy, prevention of PTB is based on identification of risk factors in obstetrical history, biochemical markers, and short cervix. Both history of PTB and asymptomatic short cervix at the second trimester are good predictors of PTB [7–10]. Transvaginal cervical length measurement (TVCL) at approximately 24 weeks of gestation can predict PTB before 35 weeks using a cutoff for cervical length of ≤ 25 mm with sensitivity of 37.3%, specificity of 92.2%, and positive and negative predictive values of 17.8% and 97.0%, respectively [7].

Progesterone, by its maintenance of uterine quiescence through anti-inflammatory effects, has been shown to decrease the risk of PTB in women with the aforementioned risk factors [11, 12]. In women with prior PTB, the weekly use of 250 mg of 17α-hydroxyprogesterone caproate intramuscularly could reduce the PTB rate before 37 weeks of gestation from 54.9% to 36.3% (relative risk [RR], 0.66; 95% confidence interval [CI], 0.54–0.81) [11]. In women with asymptomatic short cervix (TVCL measurement of 10–20 mm) at the second trimester, 90 mg of vaginal progesterone could effectively reduce PTB before 33 weeks from 16.1% to 8.9% (RR, 0.55; 95% CI, 0.33–0.92) [13]. Universal cervical length screening followed by treatment with vaginal progesterone has been shown to be the most cost-effective strategy for preventing PTB [14, 15]. These findings were confirmed in a meta-analysis [16].

Nevertheless, only a minority of women may benefit from progesterone treatment if it is started at the second trimester. This is because only approximately 10% of spontaneous early PTB cases were associated with a history of prior PTB [17] and approximately 5% of women had a cervical length of approximately 20 mm at 22 + 0–24 + 6 weeks of gestation [7]. Therefore, the remaining women who may have PTB may not have any identifiable risk factor. Even if physicians are able to detect these risk factors and offer progesterone treatment at approximately 16–24 weeks, 36.3% of women with a history of PTB and 30.2% of women with an asymptomatic short cervix still give birth before 37 weeks [11, 13]. There is still a large proportion of PTB, which is currently not preventable, and the current approach to preventing PTB is far from ideal. One possible hypothesis is that the initiation of progesterone treatment would be too late for its effect to take place. Early progesterone treatment may maintain uterine quiescence and prevent shortening of the cervix from early gestation [18].

### Objectives and hypothesis

#### Primary objective

The aim of this multicenter, randomized, double-blind, placebo-controlled trial is to determine whether early universal use of oral progesterone before 14 + 0 weeks of gestation can prevent PTB in singleton gestations better than universal screening of cervical length at 18 + 0 to 23 + 6 weeks of gestation, followed by progesterone treatment in those with a short cervix in a singleton pregnancy. The hypothesis is that early universal progesterone treatment from before 14 + 0 weeks could decrease the risk of PTB further than progesterone treatment in women with an asymptomatic short cervix detected by universal cervical length screening.

## Methods

### Trial design

SINPRO (Early Use of Oral Progesterone in All Women for Prevention of Preterm Delivery in Singleton Pregnancy) is a multicenter, randomized, double-blind, placebo-controlled trial that will be carried out in six public maternity units in Hong Kong: Kwong Wah Hospital, Pamela Youde Nethersole Eastern Hospital, Princess Margaret Hospital, Queen Elizabeth Hospital, Queen Mary Hospital, and United Christian Hospital. The steering committee consists of the principal investigator and co-investigators from other centers. The data management team is composed of a group of maternal and fetal subspecialists who will meet every 6 months to oversee the progress and safety of the study, which is independent from the funder and competing interests. These recruiting hospitals serve approximately 55% of the births in Hong Kong. Queen Mary Hospital is affiliated with the University of Hong Kong. The study has been approved by the Institutional Review Board of the University of Hong Kong/Hospital Authority Hong Kong West Cluster (UW 17-308) and has been registered with ClinicalTrials.gov (identifier NCT03428685). The clinical trial protocol follows the Standard Protocol Items: Recommendations for Interventional Trials (SPIRIT) 2013 checklist format (Additional file 1). If any change to the protocol is required, the funder and the ethics committee will be notified. The principal investigator will then inform the participating centers and update the information in the clinical trial registry. Deviations from the protocol will be fully documented using a breach report form. Figure 1 summarizes the trial design, and the details are described below. The study started in January 2019 and had recruited 310 subjects by 13/1/2020.

**Fig. 1 Fig1:**
[figure not shown]
Schedule of enrollment, intervention, and assessment

### Eligibility criteria

Women attending the antenatal service will be informed of this study. Research assistants will visit the participating hospitals regularly to ensure adequate subject enrollment. Women aged ≥ 18 years who have a confirmed viable singleton intrauterine pregnancy before 14 + 0 weeks of gestation will be recruited. They will have a dating scan before 14 + 0 weeks of gestation to confirm no dating problem, and the estimated date of confinement will be based on the ultrasound scan findings. Women will be excluded if they meet any of the following criteria:
MiscarriageEctopic pregnancyTwin pregnancy with miscarriage of one twinHeavy vaginal bleeding requiring surgical interventionSevere abdominal pain requiring surgical interventionPresence of feverHistory of adverse reaction to progesteroneHistory of breast or genital tract malignancyHistory of suspected thromboembolic diseaseCongenital uterine anomalyUnwillingness or inability to comply with study proceduresKnown paternal or maternal abnormal karyotype

Women who are willing to join the study will sign the consent form prior to any procedures being done. The investigators will sign the consent form. The consented women can withdraw their consent at any time without affecting the standard medical care they receive. On the consent form, participants will be asked for permission for the research team to share relevant data with people from the hospitals taking part in the research or from regulatory authorities, where relevant. This trial involves collecting biological specimens for storage.

### Randomization and masking

The randomization process will be done in a 1:1 ratio by a research nurse not involved in the women’s clinical care, using a computer program. The result of each randomized participant will be put in a sequentially numbered, opaque, sealed envelope. One envelope will be opened if a woman agrees to join the study. Women will be randomly assigned at the time of recruitment to one of the two groups on the day of first TVCL measurement before 14 + 0 weeks of gestation:
*Treatment group*: dydrogesterone 10 mg three times daily (Abbott Biologicals B.V., Olst, The Netherlands)*Placebo group*: placebo identical to the active drug in external appearance but without an active ingredient

Participating women, attending clinicians, study investigators, and study coordinators are blinded to the group assigned.

### Procedure

Ultrasonographers must attend the “Cervical Assessment” online lecture and obtain the certificate of competence from the Fetal Medicine Foundation website. TVCL will be measured using a standard protocol [19]. Women will be asked to empty the urinary bladder before the TVCL measurement. A transvaginal ultrasound probe will be inserted into the vagina and directed into the anterior fornix. A sagittal view of the cervical canal will be obtained, and excessive pressure on the cervix will be avoided. Cervical length will be defined as the linear measurement of the cervical canal between the V-shaped internal and external os, surrounded by the hypoechoic endocervical mucosa. The shortest distance between the three measurements will be recorded. If uterine contraction is observed in the lower segment close to the internal os, ultrasound will be repeated after 5–10 min when the contraction ceases. After the baseline cervical length assessment, women will be instructed to take the oral progesterone or placebo accordingly, three times per day, from 12 + 0 to 14 + 0 weeks to 36+ weeks of gestation.

A second TVCL assessment will be performed between 18 + 0 weeks and 23 + 6 weeks of gestation. On the basis of available evidence of progesterone treatment in women with asymptomatic short cervix [12], women in the assigned group will be unblinded if the TVCL measurement is ≤ 25 mm. The women receiving placebo will be given the option of oral progesterone (10 mg three times per day) or vaginal progesterone 200 mg daily (Endometrin, Ferring Pharmaceuticals Inc., Parsippany, NJ, USA; or Utrogestan, Besins Healthcare, Monaco) until 36+ weeks of gestation (or cervical cerclage if the women has a history of preterm delivery or second-trimester miscarriage) [20]. For women in the progesterone group whose cervical length is ≤ 25 mm at 18 + 0 to 23 + 6 weeks of gestation, options will be offered of continuation of oral progesterone (10 mg three times per day), vaginal progesterone 200 mg daily (Endometrin or Utrogestan), or cervical cerclage if the women have a history of PTB.

Progesterone level will be obtained at the time of recruitment, between 18 + 0 and 23 + 6 weeks, and between 28 + 0 and 31 + 6 weeks of gestation. Serum will be drawn at the time of recruitment for further analysis. Participating women will be asked to return the empty drug packaging at follow-up to check for compliance and to remind them to complete the follow-up. Adverse effects from the medication will also be noted. Satisfactory compliance will be defined as taking at least 80% of prescribed medication. Treatment will be stopped if there is rupture of membranes or established preterm labor (cervical dilation ≥ 3 cm). Women will be followed up at the antenatal clinic as scheduled and managed according to departmental protocol. During and after the study period, subjects will be managed by the investigators, who have ample experience in looking after obstetric patients and managing them throughout their pregnancy. There is no compensation for trial participation.

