#### Obstetric outcomes

Spontaneous PTB before 37 + 0 weeksPTB before 32 + 0 weeksPTB before 28 + 0 weeksPreterm prelabor rupture of membrane (rupture of membrane before 37 + 0 weeks, confirmed clinically by [a] oozing of liquor from the external cervical os, [b] pooling of liquor at the posterior fornix, or [c] decreased liquor on ultrasound with history suggestive of leaking)Spontaneous miscarriage before 20 + 0 weeksStillbirth: fetus dies in utero after 24 + 0 weeksCervical length at 18 + 0 to 23 + 6 weeksGestational age at birthMode of delivery

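### After a short cervix is found, the history that qualifies a woman for cerclage is worded more broadly for placebo than for progesterone

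*Protocol article*

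**What the plan says.** The Procedure section of the protocol article sets one trigger for both arms: cervical length of 25 mm or less between 18+0 and 23+6 weeks, followed by unblinding. It then lists the options for each arm in turn.

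- Placebo arm: oral or vaginal progesterone, or "cervical cerclage if the women has a history of preterm delivery or second-trimester miscarriage".
- Progesterone arm: continued oral progesterone, vaginal progesterone, "or cervical cerclage if the women have a history of PTB".

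The Methods paragraph of the Abstract describes the same step without separating the arms: "the management option for short cervix will be discussed (oral progesterone, vaginal progesterone, or cervical cerclage". It gives no history condition. Later in Procedure, general antenatal care is to be "managed according to departmental protocol", again without a criterion for cerclage.

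**The concern.** Two consecutive sentences give different eligibility for the same procedure after the same trigger, and the article does not explain the difference. Cerclage is aimed at the primary outcome, preterm birth, and the choice is made after allocation has been revealed. A rule that depends on arm at that point makes a co-treatment differ by allocation. What is at stake is mainly equal care for women with the same cervix and the same history, together with a small, avoidable difference between the arms in a treatment that may affect the primary outcome. A site reading the article cannot tell which criterion applies to a progesterone woman with a previous second-trimester loss.

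**Working it through.** **The plan's own figure.** The Sample size estimation section gives 814 per group for 6% versus 3%, 80% power and 5% significance with Fisher's exact test. Taking the test as two-sided, the normal-approximation formula for two proportions gives 749 per group without continuity correction and 814 with it, so the figure reproduces. Exact Fisher power at 814 per group is 0.809. With 5% attrition, 814 / 0.95 = 856.8, that is 857 per group. None of this depends on the cerclage wording.

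**Who falls in the gap.** Background and rationale has preterm birth "defined as birth before 37 completed gestational weeks", with no lower limit. A late second-trimester loss could therefore already count as prior preterm birth. Obstetric outcomes lists "Spontaneous miscarriage before 20"+0 weeks as a separate event. On the narrowest reading, the gap is a progesterone-arm woman whose only qualifying history is a second-trimester loss before 20+0 weeks. Obstetric outcomes dates stillbirth from 24+0 weeks, so a site that does not count a loss at 20 to 23 weeks as preterm birth would face a somewhat wider gap.

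**Inputs from the article**
- Short cervix: 4.6% (Sample size estimation). This is for less than 25 mm in the local population, whereas the trial rule is 25 mm or less, and early progesterone may lower the figure in the active arm.
- Group size: 814 to 857 (Sample size estimation).
- Preterm birth risk with a short cervix on treatment: "30.2% of women with an asymptomatic short cervix still give birth before 37 weeks" (Background and rationale). The source population is described there as "In women with asymptomatic short cervix (TVCL measurement of" 10–20 mm, given vaginal progesterone. It may not fit all women at or below 25 mm, so a range of 20–40% is used.

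**Assumed inputs (not in the article)**
- Share of short-cervix women with a second-trimester loss and no preterm birth: 1–10%.
- Relative reduction in preterm birth by cerclage: 25–50%.
- Uptake of cerclage if offered: 50–100%.

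**Formulas**
- Affected women = n × 0.046 × share.
- Extra preterm births = affected women × risk × reduction × uptake.
- Shift in the arm's rate = extra preterm births / n.

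**Results**
- Short-cervix women per arm: 0.046 × 814 = 37.4; 0.046 × 857 = 39.4.
- Affected women: 37.44 × 0.01 = 0.37; 39.42 × 0.10 = 3.94.

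| Case | Calculation | Extra preterm births | Shift (percentage points) |
|---|---|---|---|
| Low | 37.44 × 0.01 × 0.20 × 0.25 × 0.5 | 0.009 | 0.009 / 814 = 0.001 |
| Middle | 39.42 × 0.05 × 0.302 × 0.5 × 0.5 | 0.15 | 0.15 / 857 = 0.017 |
| High | 39.42 × 0.10 × 0.40 × 0.50 × 1.0 | 0.79 | 0.79 / 857 = 0.09 |

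The planned difference is 3 points. The high case sets every input at its maximum and supposes that no clinician offers cerclage to an affected progesterone woman.

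**The case against.** The strongest reply is that this is a drafting shortcut. The progesterone sentence also drops the stop point, the manufacturers and the citation given for placebo. Nobody would read the missing stop point as a different stopping rule, so the missing miscarriage clause need not be a different cerclage rule. The Abstract lists the same options for everyone, options are offered rather than prohibited, and clinicians may well offer cerclage anyway. Preterm birth has no stated lower limit and might take in second-trimester loss. The 20+0 week boundary defines an outcome of the current pregnancy and is not a rule for classifying history. Finally, the article condenses Protocol 4.0, which is not shown and may be consistent.

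Most of this stands. An abbreviated repeat is the likeliest explanation, a difference in actual care is not shown, and the exact subgroup is an inference. It does not remove the inconsistency, though. The placebo sentence lists preterm delivery and second-trimester miscarriage separately, so the second is not simply contained in the first. Neither the Abstract nor the reference to departmental practice gives a common criterion. Nor is this detail left to a fuller document: the article states both criteria, and they differ.

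**Conclusion.** The point holds as a low-priority inconsistency in a stated treatment rule. As written, eligibility for a co-treatment aimed at the primary outcome depends on known allocation. The effect on the primary result is negligible: 0 to 4 women affected and a shift of at most 0.09 points in the cases examined. Those figures rest largely on the assumed history share, cerclage effect and uptake. If cerclage works, the shift disadvantages progesterone and so cannot create a false benefit. Confidence is medium, because whether sites follow the narrower wording cannot be settled from the article.

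**What to change.** In Procedure, give the progesterone arm the same history criterion as the placebo arm, covering both prior preterm delivery and prior second-trimester miscarriage. Then confirm that Protocol 4.0 (dated 3/9/2018 under Trial status), as held by the sites, says the same.

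The cost is one clause and one document check. If Protocol 4.0 already agrees, only the article wording needs correcting. If it carries the same mismatch, a short amendment and a note to sites are needed. With 310 of 1714 women recruited by 13/1/2020, most of the planned women had yet to be enrolled at that date and would be covered by the correction. Sample size and analysis stay as they are.

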### Outcomes

The primary outcome is the rate of PTB **(**defined as birth before 37 + 0 gestational weeks). Outcomes will also be evaluated for subjects who discontinue or deviate from the protocol. Other secondary outcomes and their definitions are as follows:

#### Obstetric outcomes

Spontaneous PTB before 37 + 0 weeksPTB before 32 + 0 weeksPTB before 28 + 0 weeksPreterm prelabor rupture of membrane (rupture of membrane before 37 + 0 weeks, confirmed clinically by [a] oozing of liquor from the external cervical os, [b] pooling of liquor at the posterior fornix, or [c] decreased liquor on ultrasound with history suggestive of leaking)Spontaneous miscarriage before 20 + 0 weeksStillbirth: fetus dies in utero after 24 + 0 weeksCervical length at 18 + 0 to 23 + 6 weeksGestational age at birthMode of delivery

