### Statistics

#### Statistical tests

##### Analysis plan

All statistical analyses will be carried out using SAS version 9.2 or above (SAS Institute, Cary, NC, USA) and/or R version 3.2.0 or above (R Foundation for Statistical Computing, Vienna, Austria) or IBM SPSS Statistics software (IBM, Armonk, NY, USA).

The primary analysis will be evaluated by Fisher’s exact test to compare the difference of PTB rates between the progesterone and control groups. The analysis will primarily be carried out according to intention-to-treat and per-protocol principles. The intention-to-treat analysis will include any randomized subjects with nonmissing primary outcome data. The per-protocol analysis will include all randomized subjects in the intention-to-treat analysis who have sufficient treatment compliance (≥ 80%) and no major protocol deviations.

Nominal data will be described by frequencies and percentages, and correlations will be analyzed using the chi-square test; continuous data will be expressed as mean ± standard deviation or median (range) and analyzed using Student’s *t* test or the Mann-Whitney *U* test, depending on the normality of the data. Logistic regression analysis will be applied to evaluate the association between PTB and the effect of early universal use of progesterone, history of previous PTB, cervical length measurement at 18 + 0 to 23 + 6 weeks of gestation, serum progesterone level, and other risk factors, if appropriate. The interaction effect will be evaluated to assess the impact of the history of previous PTB or cervical length on treatment effect. A *P* value < 0.05 will be considered as statistically significant. Interim analysis will be done when the primary outcome is available for 850 subjects (~ 50% of the intended recruitment), and the trial will be stopped if there is a significant difference in the PTB rate between the two groups.

The research assistants will be responsible for data entry. Hard copies will be locked in a cabinet during the course of the study, and the electronic copy will be encrypted/password-protected. The data collected during the course of the research will be kept strictly confidential and will be accessible only by members of the trial team. Anonymized trial data can be shared with other researchers to enable international meta-analyses.

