#### Sample size estimation

The PTB rate of singleton pregnancy at 37 weeks of gestation in Hong Kong is approximately 6.5% [21]. Among the local population, 4.6% had cervical length < 25 mm [22]. The use of universal screening of cervical length followed by treatment with vaginal progesterone in those with a short cervix would further bring down the rate to 6% [23]. Treatment with progesterone is anticipated to further reduce this proportion by an absolute difference of 3%. A sample size of 814 per group is required to achieve power of 80% power at the 5% significant level based on Fisher’s exact test. Assuming an attrition rate of 5%, a total of 1714 subjects (857 subjects per group) will be recruited.

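### Fetal loss at 20+0 to 23+6 weeks belongs to neither loss outcome, and the article does not fix whether such a loss counts as preterm birth or as missing.

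*Protocol article*

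**What the plan says.** All references are to the protocol article.

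- **Obstetric outcomes.** The loss outcomes stand next to each other (list separators were lost when the text was read): "Spontaneous miscarriage before 20 + 0 weeksStillbirth". Stillbirth is then defined as in-utero death after 24+0 weeks. The same list has spontaneous preterm birth (PTB) before 37+0, PTB before 32+0, PTB before 28+0 and gestational age at birth. None of these has a lower limit.
- **Outcomes.** The primary outcome is PTB, "defined as birth before 37 + 0 gestational weeks". The Background definition, "defined as birth before 37 completed gestational weeks", also has only an upper limit. The Outcomes section adds: "Outcomes will also be evaluated for subjects who discontinue or deviate from the protocol".
- **Procedure.** Study medication is taken "from 12 + 0 to 14 + 0 weeks to 36+ weeks of gestation". The second cervical scan is at 18+0 to 23+6, and allocation is unblinded if cervical length is 25 mm or less.
- **Analysis plan.** "The intention-to-treat analysis will include any randomized subjects with nonmissing primary outcome data". The primary comparison uses Fisher's exact test, and one interim look is planned once the primary outcome is known for 850 women.

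**The concern.** The two loss definitions do not meet. Miscarriage stops at 20+0 and stillbirth begins after 24+0, so a fetal death in the four weeks between has no place in the loss tables. If the plan is followed exactly, fetal loss after randomization is undercounted in both arms.

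The primary outcome does not settle where these losses go. With no lower limit, a delivery at 21 weeks can be read as a birth before 37+0. It can also be read as a pregnancy with no birth outcome, and the intention-to-treat rule then removes the woman as missing. The same choice arises for a loss at, say, 16 weeks, although that one is at least recorded as a miscarriage.

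What is at stake is mainly bias. Treatment starts by 14+0, and the Background argues that early progesterone may act on the uterus and cervix from early gestation, so mid-trimester loss could respond to treatment. Removing such losses conditions the comparison on a post-randomization event. The gap also falls in the weeks when some women are unblinded, so some losses might be classified with allocation known.

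**Working it through.** **1. The definitions side by side**

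| Gestation of loss after randomization | Miscarriage | Stillbirth | PTB before 37+0, 32+0, 28+0 |
|---|---|---|---|
| Start of treatment to 19+6 | yes, if spontaneous | no | yes if every delivery is a birth, otherwise not stated |
| 20+0 to 23+6 | no | no | yes if every delivery is a birth, otherwise not stated |
| After 24+0 | no | yes, if death in utero | yes, by the same wording |

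The middle row is the gap. It covers the last four of the six weeks in the 18+0 to 23+6 scan window.

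**2. The plan's own figure**

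Inputs from Sample size estimation: 6% v 3%, 5% level, 80% power, Fisher's exact test. I take the test as two-sided, which reproduces the stated figure.

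- Uncorrected: n = [1.960 × √(2 × 0.045 × 0.955) + 0.842 × √(0.06 × 0.94 + 0.03 × 0.97)]² / 0.03² = 748.4, so 749 per arm.
- With continuity correction: (748.4/4) × [1 + √(1 + 4/(748.4 × 0.03))]² = 813.7, so **814** per arm, as stated.
- With 5% attrition: 814/0.95 = 856.8, so 857 per arm and 1714 in total, as stated.
- Exact two-sided Fisher power at 814 per arm, by enumeration: **80.9%**.
- Planned events: 814 × 0.06 ≈ 49 v 814 × 0.03 ≈ 24.

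The sample size is not in error.

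**3. Losses counted as events**

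The loss rate is an assumption, because the article gives none. I use 0.5% and 1.0% of women, which is 814 × 0.005 ≈ 4 and 814 × 0.01 ≈ 8 per arm without a treatment effect. I add them to the planned rates, which also assumes that the 6% does not already include them.

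| Assumed loss | Treatment does not affect losses | Power | Treatment halves losses | Power |
|---|---|---|---|---|
| 0.5% | 6.5 v 3.5% | 76.7% | 6.5 v 3.25% | 84.3% |
| 1.0% | 7.0 v 4.0% | 72.9% | 7.0 v 3.5% | 87.2% |

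**4. Losses treated as missing**

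- Same loss rate in both arms: 810 or 806 women per arm remain, and power at 6 v 3% is 80.7% or 80.5%. Almost no power is lost.
- Limiting case of bias: treatment prevents loss in 0.5% of women and every one of them then delivers preterm. The observed contrast is about 6.0 v 3.5%, a difference of 2.5 instead of 3 points, and power is 62.2%. A benefit would be scored as harm.

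**The case against.** **The losses are not lost to the trial.** PTB has no lower limit, so a delivery at 20+0 to 23+6 literally enters PTB before 37+0, 32+0 and 28+0, and gestational age at birth. This stands. A reader might infer that these losses vanish from every outcome, and the text does not support that. What remains is that they are absent from the loss outcomes. The literal reading also counts every loss before 20+0 twice, as miscarriage and as PTB.

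**Nothing says that losses will be dropped.** This also stands. The Outcomes section says that women who discontinue are still evaluated. Exclusion is a reading that the intention-to-treat wording permits, not one that it states.

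**An article condenses a fuller protocol.** The handling of terminations and the exact coding of missing outcomes may well be settled there, and I do not count their absence. The two loss limits are different: they are printed, and they do not meet.

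**Power need not fall.** A reader might infer that counting losses weakens the trial. That holds only if treatment has no effect on losses; if it halves them, power rises. The bias example is likewise an extreme. It needs every averted loss to end preterm, and at a 0.5% loss rate it needs all losses to be averted.

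**Making every spontaneous loss a primary event would go too far as a correction.** It would redefine the primary endpoint in a trial that is already recruiting. That is a trade-off for the investigators, and the gap does not require it.

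**Conclusion.** The point holds in a limited form. The loss outcomes leave 20+0 to 23+6 uncovered, in weeks when women are on treatment and some are being unblinded. The primary outcome and the intention-to-treat rule, as written, allow such a loss to be counted as PTB or treated as missing. If it is excluded, the comparison is conditioned on an event that treatment may affect.

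The size cannot be fixed from the article. At an assumed 0.5 to 1.0% loss counted as events, power at 814 per arm runs from 77 to 73% with no treatment effect on losses and from 84 to 87% if treatment halves them, against 80.9% as planned. If losses are dropped equally from both arms, power hardly moves and bias is the issue. The documents do not support a claim that the trial is underpowered for this reason, or that losses will in fact be dropped.

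**What to change.** 1. Make the loss outcomes contiguous, so that every loss after randomization is reported by arm.
2. State one lower gestational limit for PTB, and do so before the interim look at 850 women. The choice of limit is for the investigators.
3. Keep every randomized woman with a known pregnancy outcome in the intention-to-treat denominator, so that a pregnancy loss is not coded as a missing outcome.
4. Add one sensitivity analysis of spontaneous loss or birth before 37+0. If losses already count in the primary outcome, use one limited to births from 24+0 instead.

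The cost is new wording in Outcomes and Analysis plan and slightly more analysis and reporting. The article does not say that the gestation and nature of every loss are recorded, so the data forms should be checked for both.
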